### Primary and secondary outcomes

The primary (efficacy) outcome is the proportion of recurrent, clinically symptomatic, objectively confirmed VTE within 90 days of randomisation, defined as recurrent PE or lower limb DVT.^50 51^ The objective diagnostic criterion for PE, based on available radiographic reports, is a new intraluminal filling defect on CTPA or pulmonary angiography; a perfusion defect involving at least 75% of a segment, with corresponding normal ventilation (ie, high probability lung scan); the confirmation of new PE at autopsy; or objectively confirmed proximal DVT of the lower extremity in patients with symptoms of PE. The objective diagnosis of DVT is the non-compressibility of a venous segment on CUS or an intraluminal filling defect on contrast venography. Because compression of iliac veins and the inferior vena cava may be technically difficult, additional diagnostic criteria for iliac and caval DVT also include abnormal duplex flow patterns compatible with thrombosis or an intraluminal filling defect on CT or MRI venography.^52^ Both proximal and distal DVTs are considered.

Separate secondary (safety) outcomes include the proportion of clinically significant bleeding and all-cause mortality 90 days following randomisation. Clinically significant bleeding is a composite endpoint of major and clinically relevant non-major bleeding. Major bleeding is defined as fatal bleeding, symptomatic bleeding at critical sites (intracranial, intraspinal, intraocular, retroperitoneal, intra-articular, pericardial or intramuscular with compartment syndrome), or bleeding with a reduction of haemoglobin ≥20 g/L, or bleeding leading to transfusion of ≥2 units of packed red blood cells according to the definition of the International Society on Thrombosis and Haemostasis.^53^ Clinically relevant non-major bleeding is defined as overt bleeding that does not meet criteria for major bleeding but is associated with a medical intervention, unscheduled physician contact (visit or telephone call), temporary cessation of the study drug, pain or impairment of activities of daily life.^54^

Information about the date, type and circumstances of outcome events is obtained from patients, family members, and/or healthcare providers during the follow-up interviews or by reviewing medical charts. In patients who experience recurrent VTE, the radiographic report and images confirming VTE recurrence are obtained. For patients who died during follow-up, the cause of death based on medical reports, death certificates and autopsy reports (if available) is recorded. All medical outcome events are reviewed and adjudicated by a committee of three independent clinical experts unaware of treatment assignment. Based on available information, death is adjudicated as PE-related, due to major bleeding (any death following an intracranial haemorrhage or a bleeding episode leading to haemodynamic deterioration), due to another cause or due to an undetermined cause. Death is considered PE-related in the following situations: (1) autopsy-confirmed PE in the absence of another more likely cause of death, (2) objectively confirmed PE within the last 48 hours before death in the absence of another more likely cause of death or (3) PE is not objectively confirmed, but is most likely the main cause of death.^55^ Final classification of all medical outcomes is based on the full consensus of the committee.

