Outcomes	Primary outcome: *recurrent, clinically symptomatic, objectively confirmed VTE* within 90 days of randomisation, defined as recurrent fatal or non-fatal PE or lower limb DVT (efficacy). Secondary outcomes: *clinically significant bleeding and all-cause mortality* at 90 days of randomisation (safety). Ancillary outcomes: *health-related quality of life, functional status and medical resource utilisation* at 90 days of randomisation. In a post-hoc analysis, *radiological interobserver agreement* for SSPE will be assessed.

DVT, deep vein thrombosis; ED, emergency department; PE, pulmonary embolism; SSPE, subsegmental pulmonary embolism; VTE, venous thromboembolism.

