PEmb-QoL dimension scores at 30 and 90 days as well as the change in scores from baseline will be presented by treatment group as means with 95% CIs. The change in dimension scores and the differences in the change between groups will be analysed using a repeated-measures, linear mixed-effects model adjusted for the respective baseline value. Functional status, which is measured on a scale from 0 (no functional limitations) to 5 (death) at 90 days, will be presented as median and IQR and compared between groups using the non-parametric Wilcoxon rank-sum test. Count data (subsequent hospitalisations, outpatient visits) will be presented by treatment group as rate with an exact 95% Poisson CI and compared using a rate ratio and exact p value. Time-to-event outcomes (initial LOS, time to return to work/usual activities) will be presented as medians and IQRs. For LOS, we will compare groups using the Wilcoxon rank-sum test. For return to work, we will display Kaplan-Meier curves and compare groups by the log-rank test. An alpha level of <0.05 will define statistical significance.

In secondary analyses, we will calculate the cumulative incidence and the difference in cumulative incidence of VTE recurrence and clinically significant bleeding, correcting for withdrawals and losses to follow-up by censoring and for death unrelated to VTE recurrence or bleeding as a competing event. All-cause mortality will be assessed likewise, however, a competing event does not apply. In a further secondary analysis, we will use model-based approaches for all outcomes. For time-to-event outcomes (VTE recurrence, clinically significant bleeding, LOS, return to work/usual activity), we will use competing risk regression according to Fine and Gray,^70^ accounting for non-VTE/non-bleeding-related death or all-cause death as a competing event. For mortality, we will use Cox regression. For count data, we will use a negative binomial model, and also consider zero-inflation. In case of heterogeneity across sites, we will adjust models for site using random-effects models.

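### A death adjudicated as PE-related without objective confirmation has no defined place in the primary outcome or in the cumulative-incidence analysis

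*Protocol article*

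**What the plan says.** Under Primary and secondary outcomes, the protocol article defines the primary outcome as "the proportion of recurrent, clinically symptomatic, objectively confirmed VTE within 90 days of randomisation, defined as recurrent PE or lower limb DVT". It then lists what confirms a PE: CT or conventional pulmonary angiography, a high-probability lung scan, "the confirmation of new PE at autopsy", or a confirmed proximal leg DVT in a patient with PE symptoms. Table 1 (under Selection of patients) carries the same requirement of objective confirmation but describes the outcome as "defined as recurrent fatal or non-fatal PE or lower limb DVT (efficacy"), so it names fatal PE where the main text does not.

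The same outcomes section sets out how the blinded committee assigns a cause of death. Its sources are "medical reports, death certificates and autopsy reports (if available"). A death is PE-related in any of three situations. The third is that "PE is not objectively confirmed, but is most likely the main cause of death".

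Under Planned statistical analyses, the cumulative incidence of VTE recurrence is to be estimated "correcting for withdrawals and losses to follow-up by censoring and for death unrelated to VTE recurrence or bleeding as a competing event". The later Fine and Gray regressions cover VTE recurrence, bleeding, length of stay and return to work or usual activity, "accounting for non-VTE/non-bleeding-related death or all-cause death as a competing event". The sentence does not say which kind of death goes with which outcome.

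**The concern.** A third-situation death fails the confirmation requirement by its own definition, so as worded it does not enter the primary comparison. It also falls between the categories of the cumulative-incidence analysis. It is unconfirmed, so it is not an event. It is PE-related, so it is not the stated competing event. It is neither a withdrawal nor a loss to follow-up, so it is not censored.

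A fatal PE is the gravest way in which withholding anticoagulation could fail. Autopsy is the only confirmation route specific to a death, and the article does not assume that one is always done. The non-inferiority decision rests on VTE alone, and the interim rule for the surveillance arm also monitors recurrent VTE, so it inherits the same gap. If the rule is left open, it will have to be settled after such a death has occurred.

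**Working it through.** **Where a third-situation death goes, as written**

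| Part of the protocol article | Treatment of the death |
|---|---|
| Primary outcome, main text and Table 1 | Not an event (no objective confirmation) |
| Cumulative incidence of VTE | Not an event, not a competing event, not censored |
| Fine and Gray regression for VTE | Unclear; at most a competing event, if all-cause death is the one applied to VTE |
| Attrition in the sample size | Not included (only deaths from causes other than VTE are) |
| All-cause mortality | Counted |

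**Inputs for the size of the effect** (Sample size calculation; Planned statistical analyses): 1.0% risk in both arms, margin 3.5%, one-sided 95% Agresti-Caffo upper limit, 138 per arm with 5% attrition, power of at least 80%.

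**Formula.** With x events among n in an arm, p = (x + 1)/(n + 2). Upper limit = p_S − p_C + 1.645 × √[p_S(1 − p_S)/(n_S + 2) + p_C(1 − p_C)/(n_C + 2)], where S is surveillance and C is anticoagulation.

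**The plan's own figure.** Summing exact binomial probabilities over all results with an upper limit below 3.5% gives 80.8% power at 131 evaluable patients per arm, and 131/0.95 = 137.9, so 138 per arm. The stated sample size is reproduced. Expected events are 131 × 0.01 = 1.3 per arm.

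**One added surveillance event, worked at 131 per arm**
- 2 v 1: p_S = 3/133 = 0.0226, p_C = 2/133 = 0.0150, difference 0.0075, standard error 0.0166. Upper limit 3.49%: non-inferior.
- 3 v 1: p_S = 4/133 = 0.0301, difference 0.0150, standard error 0.0182. Upper limit 4.49%: not shown.

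**Results on the boundary** (surveillance v control)

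| Evaluable per arm | Before | Upper limit | After one more | Upper limit |
|---|---|---|---|---|
| 131 | 1 v 0 | 2.88% | 2 v 0 | 3.95% |
| 131 | 2 v 1 | 3.49% | 3 v 1 | 4.49% |
| 138 | 1 v 0 | 2.74% | 2 v 0 | 3.76% |
| 138 | 2 v 1 | 3.32% | 3 v 1 | 4.27% |

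**How often a result lies on the boundary.** At 131 per arm, the largest surveillance count that still passes is 1, 2, 2, 3 and 3 for 0, 1, 2, 3 and 4 control events. With 1% risk in both arms, those pairs have probabilities 0.0951, 0.0826, 0.0542, 0.0102 and 0.0033; the next two pairs (5 and 6 control events) add 0.0003 and 0.0001. The sum is 0.2458. As a share of all non-inferior results this is 0.2458/0.8081 = 30%. The other 70% survive one added event, including 1 v 1, which becomes 2 v 1 at 3.49%.

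**Direction.** The same rule applies to both arms. Leaving out a control-arm death works against non-inferiority: at 131 per arm, 3 v 3 passes (3.45%) and 3 v 2 fails (3.98%).

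**Illustration on an assumption not in the article.** Let the true risks be 4.5% and 1.0%, so that the difference equals the margin, and let the same share of events go uncounted in both arms. The chance of declaring non-inferiority at 131 per arm is then 6.5%, 9.1%, 12.6% and 17.4% for shares of 0%, 10%, 20% and 30%.

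**The case against.** The strongest reply is that these are two definitions for two purposes: a strict endpoint, and a broader classification of cause of death. On that view the remaining text already shows the intent. Table 1 names fatal PE. Attrition takes in only deaths from causes other than VTE. The competing event leaves out VTE-related deaths. That partition is complete if an adjudicated PE-related death counts as a VTE event. Mapping adjudicated deaths to endpoint events could also sit in an adjudication charter or analysis plan that is not shown.

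The point about intent stands, and it supports the proposed fix. It does not remove the problem, because the requirement of objective confirmation is explicit in both places and the third situation is defined by its absence. This is a conflict between rules that the article states, and no omitted detail is needed to see it.

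Three stronger inferences are tempting, and the document does not support them:
- That Table 1 and the main text give different event counts. Both require objective confirmation, so read literally they agree; the conflict is with the death rules.
- That a single death decides the trial. About 70% of non-inferior results would survive one added surveillance event.
- That omission always favours surveillance. This depends on the arm in which the deaths occur.

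It is also true that the death is not lost altogether, since all-cause mortality is a secondary outcome; that the cumulative-incidence analysis is secondary; and that the committee may class a death as of undetermined cause, in which case the proposed definition would not capture it.

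**Conclusion.** The point holds as an inconsistency in the endpoint definition that should be corrected. As written, a PE-related death without objective confirmation is outside the primary outcome and has no status in the cumulative-incidence analysis. The Fine and Gray wording would at most make it a competing event, which still does not count it as VTE.

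The probability is low: patients at high risk of recurrence are excluded, and the article gives no frequency for such deaths. The consequence can be large: if one occurs on surveillance, counting it would reverse about 30% of otherwise non-inferior results. That figure rests on 1% risk in both arms, 131 evaluable patients per arm and the stated Agresti-Caffo rule; at 138 per arm the boundary results in the table reverse in the same way. The stated sample size is not affected. The article does not show that such deaths will in fact be left out, only that its wording would leave them out.

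**What to change.** Define the primary event as objectively confirmed symptomatic VTE, or death adjudicated as PE-related under any of the three situations. Use the same wording in Table 1 and the outcomes section. Use the same event in the cumulative-incidence and Fine and Gray analyses, and say which deaths compete with VTE in each. Apply it to the interim monitoring of recurrent VTE as well. Add a sensitivity analysis restricted to objectively confirmed events.

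If the sponsor prefers to keep these deaths out of the primary outcome, the article should say so and state how they enter the competing-risk analyses.

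The cost is a few sentences. No new data are needed, because the blinded committee already adjudicates every death. The downside is that a death of uncertain cause may occasionally be counted; the sensitivity analysis shows whether that matters.

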### Ancillary outcomes

Ancillary outcomes include health-related quality of life and functional status, both important patient-centred outcomes and medical resource utilisation, an economically relevant efficiency measure. Disease-specific, health-related quality of life at baseline, 30 and 90 days after the index PE is assessed using the Pulmonary Embolism Quality of Life (PEmb-QoL) questionnaire.^56 57^ The PEmb-QoL is a validated, self-administered 40-item questionnaire to quantify quality of life in patients having experienced PE. Functional status is measured at 90 days after randomisation using the post-VTE functional status scale.^58 59^ This scale has been proposed to assess functional limitations after VTE, covering aspects of daily life (including limitations in usual activity and changes in lifestyle) that are affected by the consequences of VTE and its complications. The assessment is done using a short, structured interview 90 days after randomisation.

The following measures of medical resource utilisation and productivity are assessed^44 60^: initial length of stay (LOS), subsequent overall hospitalisations as well as overall ED and physician outpatient visits within 90 days of randomisation, and time to return to work in workers or usual activities (eg, household) in non-workers. Information on these outcomes are obtained from the participant during the follow-up interviews, by interview of the patient’s primary care physician and by hospital chart review. Subsequent healthcare contacts are classified as potentially related to VTE if a patient had chest or leg symptoms or signs (dyspnoea, chest pain, pleural effusion or leg pain or swelling), or bleeding complications.

### Withdrawals and loss to follow-up

Given the low treatment and follow-up burden and the short follow-up period of 90 days, we expect that completeness of follow-up data collection will be close to 100% based on prior experience.^44^ A patient who withdraws consent for follow-up at 10 or 30 days may still agree with passive follow-up (ie, that study personnel may collect follow-up information from medical records of the participant’s primary care physician) or to continue with the assessment at 90 days, if given the option. If study withdrawal occurs, data collected up to the time of withdrawal is used in a coded manner. If a participant is lost to follow-up, primary care physicians and surrogates are contacted, and the hospital records are consulted to obtain information about primary and secondary outcomes and survival status.

### Post-hoc evaluation of radiological interobserver agreement

CTPA images undergo central review at the Bern University Hospital by a panel of two experienced thoracic radiologists blinded to the interpretation of the radiologist at the enrolling site. Based on the consensus of this panel, the initial CTPA readings are classified into three categories: (1) presence of isolated SSPE (true-positive isolated SSPE), (2) absence of any PE (false-positive isolated SSPE) and (3) presence of segmental, lobar or central PE (false-negative higher level PE). The panel also evaluates the technical quality of the CTPA examination (adequacy of opacification, breathing artefacts) and the number of filling defects (ie, single vs multiple isolated SSPE). Confirmation of the SSPE diagnosis prior to enrolling the patient is logistically not feasible due to the short timeline between diagnosis and enrolment, and it would not reflect real-world practice, thus limiting the external validity of our study results. Therefore, the central review of CTPA images is done post-hoc in 6-month batches.

### Sample size calculation

Assumptions on VTE recurrence risk are based on data from 127 low-risk patients with isolated SSPE who received anticoagulants (warfarin or low-molecular-weight heparin), showing a VTE recurrence risk of 0.8% at 90 days after diagnosis.^23^ We chose an absolute non-inferiority margin of 3.5% on the basis of recruitment feasibility, clinical acceptability and previous studies. This corresponds to a difference which is considered acceptable by most physicians and patients for the following reasons. First, our margin is within the range of the 3-month VTE recurrence proportion (0.5%–5%) below which thrombosis specialists would not initiate anticoagulation for PE.^61^ Second, the definition of a clinically acceptable non-inferiority margin for recurrent VTE must also take into account the potential benefits of withholding anticoagulation, that is, the substantially lower risk of clinically significant bleeding (<1% vs 7% within 3 months for patients receiving anticoagulants).^5 23 25 62^ Indeed, a patient group with PE who was involved in the trial planning process indicated that given the bleeding risk associated with anticoagulants, a VTE recurrence proportion of <5% seemed acceptable. Finally, similar non-inferiority margins (3%–5%) have been used in key studies comparing different drug treatment regimens and inpatient versus outpatient management for acute VTE.^42 44 63–67^

To determine the sample size, we used a Monte-Carlo simulation approach based on an Agresti-Caffo CI for risk difference.^68^ Assuming a baseline VTE recurrence proportion of 1.0% at 90 days in both treatment groups, an absolute margin of 3.5% defining non-inferiority for clinical surveillance and a sampling ratio of 1:1 allowing 5% attrition (dropouts, including patients who died from non-VTE-related causes) in each group during 90 days, we estimated that 276 patients (138 per group) would result in at least 80% power to establish non-inferiority at an one-sided type I error of 5%.

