### Planned statistical analyses

As recommended by the Consolidated Standards of Reporting Trials statement for non-inferiority trials,^69^ we will perform both intention-to-treat (ITT) and per-protocol (PP) analyses. For the primary outcome, ITT and PP analyses should reach the same conclusion to consider results to be robust. For the remaining outcomes, the ITT analysis will be the primary analysis, the PP analysis a secondary analysis.

In the ITT analysis, all randomised patients will be analysed within the treatment group to which they were randomised. In the PP analysis, patients with protocol violations will be excluded (crossover to study treatment from other group; patients receiving a different type or dose of anticoagulation than requested by the study protocol; patients with missing primary outcome data; patients violating relevant eligibility criteria; patients stopping study treatment within 1 month after randomisation, or patients in whom the diagnosis of isolated SSPE was refuted by the central CTPA review panel).

We will describe the prevalence of recurrent VTE, clinically significant bleeding (including its individual components, major and clinically relevant non-major bleeding), and all-cause mortality at 90 days after randomisation with 95% Wilson CIs by treatment group. Non-inferiority of the primary outcome (VTE recurrence) among patients in the clinical surveillance versus the anticoagulation group will be assessed based on the Agresti-Caffo CI for risk difference.^68^ If the upper limit of the one-sided 95% Agresti-Caffo CI will be lower than the prespecified non-inferiority margin, clinical surveillance will be considered non-inferior to anticoagulation. For secondary outcomes, we will calculate the risk difference with a two-sided 95% Agresti-Caffo CI and compare groups using an exact binomial test.^68^

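### The 80% power reproduces at 131 evaluable per arm, but the decision rule's actual one-sided size there is 6.5%, not 5%, and one more surveillance-arm loss lowers power to about 73%

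*Protocol article*

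**What the plan says.** The article's section on sample size calculation gives these planning inputs:

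- Event rate: "Assuming a baseline VTE recurrence proportion of 1.0% at 90 days in both treatment groups".
- Margin: "an absolute margin of 3.5% defining non-inferiority for clinical surveillance".
- Attrition: "a sampling ratio of 1:1 allowing 5% attrition (dropouts, including patients who died from non-VTE-related causes) in each group during 90 days".
- Method: "we used a Monte-Carlo simulation approach based on an Agresti-Caffo CI for risk difference".

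From these it concludes that 276 patients, 138 per group, "would result in at least 80% power to establish non-inferiority at an one-sided type I error of 5" per cent.

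The section on planned statistical analyses makes the same interval the decision rule. Surveillance is called non-inferior "If the upper limit of the one-sided 95% Agresti-Caffo CI will be lower than the prespecified non-inferiority margin". Sizing and analysis therefore use one method consistently. The article does not give the actual type I error of that method, or say how power changes with the evaluable number.

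**The concern.** At a 1.0% rate, 131 patients per arm yield about 1.3 events (131 x 0.01). With so few events only a handful of results decide the trial. An approximate interval then need not hold its nominal level, and power moves in jumps as the evaluable number changes. The sentence in the plan presents 5% as the type I error itself and 80% as a lower bound, with no qualification.

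A type I error in this trial means declaring that withholding anticoagulation is non-inferior when recurrence is in fact 3.5 percentage points higher. The rate at which the rule makes that error, and how firmly the 80% holds, are figures that ethics committees, the monitoring board and later readers will rely on.

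**Working it through.** **Inputs.** All come from the sample size section: 138 per arm; 5% attrition, so 138 x 0.95 = 131.1, taken as 131 evaluable; 1.0% in both arms for power; margin 3.5 points, so 4.5% v 1.0% is the null boundary for size; one-sided 95% limit, z = 1.645.

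**Rule.** Let s be events under surveillance and c under anticoagulation, with n evaluable per arm. Put a = (s+1)/(n+2) and b = (c+1)/(n+2). The upper limit is

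U = a - b + 1.645 x sqrt[ a(1-a)/(n+2) + b(1-b)/(n+2) ],

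and non-inferiority is declared if U < 0.035. With unequal arms, each term uses its own n.

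**Results that pass at 131 per arm.** s ≤ 1 when c = 0; s ≤ 2 when c = 1 or 2; s ≤ 3 when c = 3 or 4; s ≤ 4 when c = 5; and so on.

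**Power and size at 131 per arm.** For each c, multiply P(c) by the probability that s is small enough to pass, then add. P(c) always uses 1.0%; P(s) uses 1.0% for power and 4.5% for size.

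| c | P(c) | passes if | contribution to power | contribution to size |
|---|---|---|---|---|
| 0 | 0.2680 | s ≤ 1 | 0.1669 | 0.0046 |
| 1 | 0.3547 | s ≤ 2 | 0.3035 | 0.0222 |
| 2 | 0.2329 | s ≤ 2 | 0.1993 | 0.0146 |
| 3 | 0.1011 | s ≤ 3 | 0.0968 | 0.0156 |
| 4 | 0.0327 | s ≤ 3 | 0.0313 | 0.0051 |
| 5 or more | – | – | 0.0104 | 0.0031 |
| Total | | | **0.808** | **0.065** |

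The plan's power is reproduced at 80.8%; a simulation of 400,000 trials also gives 80.8%. The size is 6.5%. Varying the control rate along the null boundary, its maximum is 6.8%, near a 0.55% control rate.

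**Why the power is fragile.** Take s = 2, c = 1.

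- n = 131: a = 3/133 = 0.02256, b = 2/133 = 0.01504, SE = 0.01665. U = 0.00752 + 1.645 x 0.01665 = 3.490%. Passes.
- n = 130: a = 3/132 = 0.02273, b = 2/132 = 0.01515, SE = 0.01677. U = 0.00758 + 1.645 x 0.01677 = 3.516%. Fails.

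At 131 per arm and 1.0% v 1.0%, this one result has probability 0.2329 x 0.3547 = 0.083, about 8 points of power. At 4.5% v 1.0% it has probability 0.0454 x 0.3547 = 0.016, about 1.6 points of size. Those two amounts account for nearly all of the change between 131 and 130.

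**By evaluable number (surveillance / anticoagulation).**

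| Evaluable | Power (1.0% v 1.0%) | Size (4.5% v 1.0%) |
|---|---|---|
| 131 / 131 | 80.8% | 6.5% |
| 131 / 130 | 80.7% | 6.5% |
| 130 / 131 | 72.8% | 5.1% |
| 130 / 130 | 72.7% | 5.0% |
| 138 / 138 | 79.7% | 5.5% |
| Each arm Bin(138, 0.95) | 77.3% | 5.6% |

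With equal arms, power is at least 80% at 131 to 136, below 80% at 137 to 148, and at least 80% again at every number checked from 149 to 259. If each patient is lost independently with probability 5%, the surveillance arm has fewer than 131 evaluable in 39% of trials.

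**The case against.** The strongest reply is that the plan's calculation is right. Under its own inputs exact power is 80.8%, and with complete follow-up it is 79.7%, which is 80% for practical purposes. Follow-up is expected to be nearly complete (section on withdrawals), and the intention-to-treat analysis keeps all randomised patients, so numbers near 138 are plausible; there the size is 5.5%. Agresti-Caffo is a recognised interval, prespecified and used for both sizing and analysis, and 5% is its nominal level.

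Most of this stands. A reader might infer that the trial does not deliver 80% power; the document does not support that, because the figure reproduces at the planned number. A reader might also combine the two worst figures. They do not occur together: size is 6.5% where power is 80.8%, and 5.0% where power is 72.7%. What the reply does not answer is that the sentence gives 5% as the type I error, while the rule exceeds it both at 131 and at 138 per arm.

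A second reply is that intention-to-treat and per-protocol results should agree for the findings to count as robust. If both had to pass, a simulation assuming 138 per arm in the first set and random exclusions gives a joint size of about 5.3% with 131 per arm in the per-protocol set, and about 3.6% with 124. This is fair: 6.5% belongs to a single analysis at 131 per arm. But the plan states its 5% for the one-interval rule, and per-protocol exclusions also push that set towards the numbers where power is about 73%.

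A reader might conclude, thirdly, that the decision rule must be replaced, for example by a Miettinen-Nurminen score limit. That is a debatable trade-off, not a correction. The score limit has size 4.0–4.2% at a 1.0% control rate but reaches 5.4% at another control rate with 131 per arm. Its power is about 71–72%, below the trial's target.

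**Conclusion.** The point holds as a misstatement of operating characteristics, not as an error in the sample size. At the planned 131 evaluable per arm, power is as stated (80.8%), but the actual size is 6.5% against a stated 5%, a relative excess of 30% (6.5/5 = 1.3). At 138 per arm the excess is 10% (5.5/5 = 1.1), and averaged over random 5% attrition it is 12% (5.6/5 = 1.12). The 80% is sensitive to the evaluable number, and specifically to losses in the surveillance arm: one further loss there gives 72.8%, and the average over random attrition is 77.3%.

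These figures assume independent binomial outcomes, the plan's 1.0% rate and 3.5% margin, a single analysis set, and no effect of the interim safety looks. The averaged figures also assume that losses are random and unrelated to outcome.

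**What to change.** Keep the 276 patients and the Agresti-Caffo decision rule. In the sample size section, describe 5% as the nominal one-sided level and state the exact operating characteristics by evaluable number:

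- 131 per arm: power 80.8%, size 6.5%
- 130 per arm: power 72.7%, size 5.0%
- 138 per arm: power 79.7%, size 5.5%
- random 5% attrition, on average: power about 77%, size 5.6%

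Add that the maximum size at 131 per arm is 6.8% over control rates, and that the drop in power follows losses in the surveillance arm.

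Optionally, prespecify before unblinding a score-type (Miettinen-Nurminen) limit as a sensitivity analysis, noting that it is also approximate and has about 71–72% power at 130 to 138 per arm.

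The cost is a short enumeration and a wording change, with no added patients. The downside is that the stated error rate and power become slightly less favourable.
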